## Sample size calculation

This RCT will include 200 patients undergoing THA due to hip OA. The sample size was determined through an a priori power analysis using G*Power designed to detect interaction effects in a repeated measures ANOVA for the primary outcome of pain intensity. Based on our previous work, we assumed a small to medium effect size of f=0.15 for interaction effects with α=0.05 and 1 - β=0.90, resulting in a required sample size of n=164 (4 groups).^8 10 29^

To account for potential exclusions or dropouts and to enable stratified randomisation by sex/gender into the four study arms while balancing the sex/gender of the patient featured in the video intervention, we aim to recruit a total of n=200 patients, with n=50 per group. Eligibility will be assessed consecutively for all patients scheduled for THA at the UKE (Location: Helios ENDO-Clinic, UKE).

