#### Video-based treatment expectation manipulation

Patients in two of the four groups will watch a 10-min. video containing standardised study information. The video provides insight into another patient’s experience with hip-related pain, functional impairments and the subsequent surgery.

In the first part, the clinic director welcomes the viewers and explains the course of their hospital stay. The next section features a patient demonstrating how hip pain and functional limitations affect various everyday activities. This is followed by a depiction of the same activities after the hip arthroplasty, but this time without pain or impairments, illustrating the potential impact of treatment. While the video content is identical, we prepared two different videos to account for potential gender effects, featuring both a male and a female patient. The patients featured in the video are approximately 60 years old, aligning with the target study population.^32^ Participants will be randomly assigned to watch one of the two versions. Only participants of groups 1 and 3 will be shown the video intervention (figure 1). The video is presented twice: first during the preoperative baseline visit and again on the first postoperative day to reinforce what they have learnt and to support expectation maintenance during early recovery.

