### Blinding and randomisation

The study researcher responsible for analysing the primary outcomes will remain blinded to group allocation by working with a concealed group variable (group variable with hidden label). Since the intervention involves direct delivery by the study physician, the physician must be aware of group assignment to conduct the informed consent process using augmented communication where applicable. To minimise researcher bias, only trained study physicians deliver the augmented consultations (aDOC), while standard consultations (TAU) are provided by clinicians who are not involved in the intervention. Study staff administer the video separately after the physician’s visit, ensuring that consulting physicians remain unaware of whether a participant has received it. This design intentionally introduces a potential experimenter effect, allowing for the investigation of the impact of enhanced physician-patient interaction as part of the intervention itself (‘effects of augmented communication’). Blinding of the study researcher, who is unaware of the group allocation, is designed to minimise this risk as much as possible.

Participants will be randomly assigned to one of the four study groups using a block randomisation method to ensure balanced group sizes throughout the recruitment period. The block size will be kept constant at 20 and will not be disclosed to the physicians involved in recruitment. Allocation concealment will be achieved by using sealed, opaque and sequentially numbered envelopes. Each patient will draw one envelope on inclusion, thereby determining their group assignment by chance. This procedure ensures both randomisation integrity and transparency while minimising selection bias.

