### Statistical analysis

Differences in clinical outcomes between and within groups will be assessed using ANOVA for the various outcome measures. Most outcomes in this study (e.g., pain intensity, functional scores and self-efficacy and inflammatory markers) are continuous and will be analysed as such. A small number of secondary outcomes, however, are categorical (e.g.,analgesic use) and will be analysed using appropriate methods, such as chi-square tests or logistic regression, depending on the data structure. Data analysis will follow the intention-to-treat principle and will be conducted by a researcher blinded to group assignments. If significant main and interaction effects are identified, post hoc analyses (e.g., Least Significant Difference (LSD)) will be performed. The statistical analyses will be carried out using IBM SPSS Statistics software version 27.0 (IBM Corp), with results presented as means and 95% confidence intervals unless stated otherwise. If required, adjustments for deviations from sphericity will be made using Greenhouse-Geisser or Huynh-Feldt corrections for the F-test df. A two-sided p-value of <0.05 will be considered the threshold for statistical significance in all analyses.

Missing data will be handled using multiple imputation, provided that the necessary assumptions are fulfilled. Participants with extensive missing data (e.g., no primary outcome data at any timepoint) will be excluded from the respective analysis. Alongside the intention-to-treat (ITT) approach, we will conduct a per-protocol sensitivity analysis, excluding participants who did not receive the full assigned intervention. This enables us to assess the robustness of results at different levels of complexity.

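### Sex-stratified randomisation with a balanced video version is claimed in the sample size section, but the allocation procedure has no step that delivers it, and numbered envelopes are paired with a patient draw

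*Protocol article*

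**What the plan says.** Three places in the protocol article bear on allocation, and one on analysis.

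- **Sample size calculation.** The increase from 164 to 200 patients (50 per group) is to cover exclusions and dropouts and "to enable stratified randomisation by sex/gender into the four study arms while balancing the sex/gender of the patient featured in the video intervention".
- **Blinding and randomisation.** Patients are allocated "using a block randomisation method to ensure balanced group sizes throughout the recruitment period". On the blocks: "The block size will be kept constant at 20 and will not be disclosed to the physicians involved in recruitment". On concealment: "Allocation concealment will be achieved by using sealed, opaque and sequentially numbered envelopes". On how an envelope is taken: "Each patient will draw one envelope on inclusion, thereby determining their group assignment by chance". No stratum, sex-specific list or separate envelope set is mentioned.
- **Video-based treatment expectation manipulation.** A version with a male patient and one with a female patient exist; "Participants will be randomly assigned to watch one of the two versions". Only groups 1 and 3 see a video. No link to the participant's sex, or to balance, is stated.
- **Statistical analysis.** "Differences in clinical outcomes between and within groups will be assessed using ANOVA for the various outcome measures". No covariate of any kind is named, and none is excluded.

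**The concern.** There are two separate problems of description.

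First, one section relies on stratification by sex and on balance of the video patient's sex to justify part of the sample size, while the section that staff would follow has no step that could produce either. This goes beyond condensation in a journal article: the article asserts stratification in one place and sets out a procedure without it in another.

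Second, sequential numbering and a patient draw are different mechanisms. With numbered envelopes, chance lies in the pre-generated sequence and each patient gets the next number. With a draw, chance lies in the pick. If patients really choose, the blocked sequence is no longer followed, the audit trail from list to patient is lost, and balance during recruitment is not assured.

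At stake are the sex balance that the trial claims and a verifiable allocation record. Neither can be restored for patients already randomised.

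**Working it through.** **1. The plan's own figure.** Inputs from the sample size section: "we assumed a small to medium effect size of f=0.15 for interaction effects", α = 0.05, power 0.90, k = 4 groups. The number of measurements m and their correlation ρ are not stated; m = 2 and ρ = 0.5 are assumed here. For the within-between interaction:

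- λ = f²·N·m/(1 − ρ) = 0.0225 × 164 × 2/0.5 = 14.76
- df1 = (k − 1)(m − 1) = 3; df2 = (N − k)(m − 1) = 160
- power = 0.905, and N = 164 is the smallest multiple of 4 that reaches 0.90.

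So 164 is reproduced, though other pairs also give it (for example m = 7, ρ = 0). The step to 200 corresponds to a loss of 1 − 164/200 = 18%. Nothing in this calculation depends on stratification.

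**2. Sex balance under the procedure as written.** Inputs: 200 patients, ten blocks of 20, 5 per arm per block, 50 per arm (documents); share of women (assumed). With one sequence for all patients, the number of women in an arm has SD √(50 × 0.5 × 0.5) = 3.54 at 50% women and √(50 × 0.55 × 0.45) = 3.52 at 55%. Simulated gap between the arms with most and fewest women:

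| Allocation | Women (assumed) | Mean gap | 95th percentile | Gap ≥ 10 |
|---|---|---|---|---|
| No strata | 50% | 7.3 | 13 | 23% |
| No strata | 55% | 7.2 | 13 | – |
| No strata | 60% | 7.1 | 13 | 21% |
| Blocks of 20 within each sex | 50% | 1.7 | 3 | – |
| Blocks of 20 within each sex | 60% | 1.7 | 3 | – |

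The assumed share of women hardly matters. Stratifying has a small price: with incomplete last blocks, total arm sizes differ by 2.5 on average (95th percentile 5) instead of 0.

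**3. Video version.** A block of 20 holds 5 patients in group 1 and 5 in group 3, so 10 video patients, who can be split 5/5 between versions. Over 50 per arm, 25/25 is possible. The block size is therefore no obstacle. What is missing is a rule that fixes the version in advance.

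**4. Numbered envelopes against a draw.** There are three readings:

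- *The next number is taken.* Nothing is lost, but the sentence saying that the draw determines the group by chance is wrong.
- *Choice among the current block's 20.* Each block still closes at 5 per arm, but the order and audit trail within the block are lost.
- *Choice from one pool of 200 (assumed worst case).* After 100 patients, arm sizes differ by 7 on average (95th percentile 13), against 0 with blocks followed in order.

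**5. Stratifying by sex but analysing without it.** Simulated four-group ANOVA at one time point, N = 200, 50% women (assumed), 4,000 runs per cell (Monte Carlo SE √(0.05 × 0.95/4000) = 0.003 for type I error). Power is for a 0.6 SD shift in one arm.

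| Sex effect (assumed) | Type I error, sex omitted | Type I error, sex included | Power, sex omitted | Power, sex included |
|---|---|---|---|---|
| 0.3 SD | 0.038 | 0.043 | 0.869 | 0.879 |
| 0.5 SD | 0.039 | 0.048 | 0.865 | 0.877 |
| 0.8 SD | 0.030 | 0.055 | 0.835 | 0.871 |

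Omission costs about 1 to 4 points of power. The abstract says that the primary analysis compares changes in pain. A sex effect that is constant over time cancels from within-patient change, so the loss arises only where sex affects the change itself.

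**The case against.** The strongest reply is that the randomisation section never says the list is unstratified; it is silent. Blocks of 20 can run inside sex strata, and an article may leave separate lists and envelope sets to the full protocol. On that reading the gap is 1.7 women, not 7. This stands as far as it goes: the two sections are unreconciled rather than logically incompatible, and the 7-woman figure applies only if the procedure is followed as printed. It does not remove the need to reconcile them. Likewise, *draw* may loosely mean taking the next envelope, in which case only wording is at fault.

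A reader might infer more than the documents support:

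- *Blocks of 20 cannot balance two video versions, because 5 per arm is odd.* Only the split within a single arm of a single block is odd, and no section promises balance there.
- *A constant block makes allocation predictable.* A guessing rate of about 62% requires a recruiter who knows the block size and boundaries and tracks every assignment. The plan withholds the size from recruiting physicians and does not establish that those who recruit also deliver the augmented conversation. A fixed block size, or the absence of mixed sizes, is not an error here.
- *The missing sex term is a mistake that biases the result.* The article lists no covariates at all, which is commonly left to the analysis plan, and the effect of omission is mild conservatism.

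**Conclusion.** The concern holds as a should-fix point with two parts. The article claims sex-stratified allocation with a balanced video version but describes a procedure that delivers neither. It also pairs sequential numbering with a draw by the patient.

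Followed as printed, the arms with most and fewest women would differ by about 7 on average and 13 at the 95th percentile, against about 1.7 and 3 with blocks within sex (50 per arm, 50–55% women assumed). The harm from the draw depends on the pool drawn from, which is not stated, so no single size can be given.

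A chance imbalance in sex does not invalidate a randomised comparison, and 164 and 200 stand. Including sex in the analysis is an inexpensive improvement that follows from stratifying on it, not the repair of a biased test.

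**What to change.** For patients not yet randomised, state one procedure in the randomisation section and make the sample size and video sections agree with it:

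1. Separate pre-generated blocked lists, and separate envelope sets, for women and men.
2. The video version (male or female patient) written into the list for groups 1 and 3, so that it balances within sex and across the two video arms. Blocks of 20 can be kept: for example, 3/2 in one video arm and 2/3 in the other, reversed in the next block.
3. The next-numbered envelope in the patient's set opened in order, with the reference to drawing deleted.
4. Sex and its interaction with time included in the primary repeated-measures model as the stratification factor.

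If lists of this kind are already in use, only the text and the model need changing. Otherwise the cost is new lists and envelope sets and one added model factor. The sample size is unaffected.

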### Statistical analysis

Differences in clinical outcomes between and within groups will be assessed using ANOVA for the various outcome measures. Most outcomes in this study (e.g., pain intensity, functional scores and self-efficacy and inflammatory markers) are continuous and will be analysed as such. A small number of secondary outcomes, however, are categorical (e.g.,analgesic use) and will be analysed using appropriate methods, such as chi-square tests or logistic regression, depending on the data structure. Data analysis will follow the intention-to-treat principle and will be conducted by a researcher blinded to group assignments. If significant main and interaction effects are identified, post hoc analyses (e.g., Least Significant Difference (LSD)) will be performed. The statistical analyses will be carried out using IBM SPSS Statistics software version 27.0 (IBM Corp), with results presented as means and 95% confidence intervals unless stated otherwise. If required, adjustments for deviations from sphericity will be made using Greenhouse-Geisser or Huynh-Feldt corrections for the F-test df. A two-sided p-value of <0.05 will be considered the threshold for statistical significance in all analyses.

Missing data will be handled using multiple imputation, provided that the necessary assumptions are fulfilled. Participants with extensive missing data (e.g., no primary outcome data at any timepoint) will be excluded from the respective analysis. Alongside the intention-to-treat (ITT) approach, we will conduct a per-protocol sensitivity analysis, excluding participants who did not receive the full assigned intervention. This enables us to assess the robustness of results at different levels of complexity.

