**Methods and analysis:**

This randomised controlled trial (RCT) investigates the impact of augmented physician communication and observational learning on treatment expectations and recovery. Participants (n=200) will be randomised into four groups: treatment as usual (TAU), augmented doctor conversation (aDOC), observational learning video (Video) and a combination of both (aDOC+Video). The aDOC group receives empathic communication and targeted information to strengthen self-efficacy. The Video group watches a model patient demonstrating successful recovery. The combined group receives both interventions. Outcomes will be assessed at multiple time points (4 days preoperatively; 1 and 4 days, 4 weeks and 3, 6 and 12 months postoperatively), including subjective pain ratings, mobility and objective physical function. The primary analysis will compare changes in pain intensity across groups. Secondary outcomes will include functional status, self-efficacy, recovery and systemic inflammatory markers. Statistical analysis involves repeated measures ANOVA and post hoc tests for between-group and within-group comparisons.

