### Study design

We will conduct a RCT using a 2×2 factorial design (physician communication x social observational learning, both with the levels yes/no) with repeated measurements. Patient visits and the administration of questionnaires will be done at various time points: preoperatively, 4 days before surgery (baseline), postoperatively during the hospital stay on day 1 and day 4 (discharge day), as well as at 4 weeks, 3 months, 6 months and 12 months after surgery. In addition to the intervention, patients will be provided with a pain diary and questionnaires to fill out throughout the postoperative period. The follow-up assessments are scheduled at 4 weeks, 3 months, 6 months and 12 months after THA.

The effects of both interventions will be tested on subjective and objective pain measures, including visceral and somatic pain reports (cf. in detail 3).

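### The primary pain analysis names no baseline covariate, so it forgoes free precision: about a quarter of the variance of a change score if the pre-post correlation is 0.5

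*Protocol article*

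**What the plan says.** The abstract's Methods and analysis paragraph describes the primary comparison as follows: "The primary analysis will compare changes in pain intensity across groups". It names the method: "Statistical analysis involves repeated measures ANOVA and post hoc tests for between-group and within-group comparisons". The Sample size calculation section says the trial was "designed to detect interaction effects in a repeated measures ANOVA for the primary outcome of pain intensity". The Statistical analysis section is more general: "Differences in clinical outcomes between and within groups will be assessed using ANOVA for the various outcome measures". It adds Greenhouse-Geisser or Huynh-Feldt corrections, which belong to a repeated measures ANOVA, and LSD post hoc tests.

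The Study design section sets out a 2×2 factorial ("physician communication x social observational learning, both with the levels yes/no") with a visit schedule that starts at a preoperative baseline. Table 1 lists the pain rating at T-4, daily in hospital and at T3 (one month). No section names baseline pain as a covariate, an analysis of covariance or a baseline-adjusted mixed model.

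**The concern.** A pain score taken before randomised treatment begins predicts the later score. A comparison of changes uses it by plain subtraction, which is less precise than regression on it whenever the correlation is below 1. The trial already collects this score, so the lost precision would cost nothing to recover.

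The form of the test also matters. A group-by-time test with many time levels spreads a lasting shift over many degrees of freedom. The trial's questions concern aDOC, Video and whether they combine additively or synergistically, and each of these is a single contrast at a given visit or averaged over visits. At stake is how precisely those effects are estimated, and the chance of detecting effects smaller than the one planned for.

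**Working it through.** **Inputs from the protocol.** Four groups, f=0.15, α=0.05, power 0.90, n=164 required and 200 recruited (Sample size calculation). The number of measurements m, the correlation ρ and the sphericity factor ε are not given. I assume m=2, ρ=0.5 and ε=1 because they reproduce the stated figure, and I vary ρ.

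**Step 1: reproduce n=164.** For the within-between interaction:

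- λ = f²·N·m·ε/(1−ρ), df1 = (k−1)(m−1)ε, df2 = (N−k)(m−1)ε.
- N=164: λ = 0.0225 × 164 × 2/0.5 = 14.76 on 3 and 160 df. Power is 0.905.
- N=160: power is 0.897, so 164 is the smallest balanced size reaching 0.90.
- N=200: power is 0.955.

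With the same ρ and ε, m=3, 4 and 7 would give 136, 116 and 84. The match is exact but not unique: m=3 with ε=0.75, for example, also lands near 164.

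**Step 2: same effect, baseline as covariate.** With two measurements, the group-by-time test is the F test on change scores. At f=0.15 the group effects on the post score have an SD of 2f = 0.30σ.

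- Variance of change: 2(1−ρ)σ².
- Residual variance with the baseline covariate: (1−ρ²)σ².
- Ratio: (1+ρ)/2, a reduction of (1−ρ)/2.

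| ρ | Variance reduction | Power at 164: change / adjusted | N for 90%: change / adjusted |
|---|---|---|---|
| 0.3 | 35% | 0.774 / 0.931 | 228 / 148 |
| 0.5 | 25% | 0.905 / 0.970 | 164 / 124 |
| 0.7 | 15% | 0.991 / 0.997 | 100 / 88 |

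The effect is held at 0.30σ in every row. At ρ=0.5 and N=200 the powers are 0.955 and 0.990. The gain at ρ=0.5 is therefore 6.5 points at 164 and 3.5 points at 200, equivalent to 40 of 164 patients.

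**Step 3: many time levels and a smaller effect.** Assume baseline plus five postoperative levels (four hospital days and T3), compound symmetry, ρ=0.5, N=200 and a constant postoperative effect with a group SD of 0.20σ. The matching interaction effect size is f = 0.20 × √5/6 = 0.075, half the planned value.

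- Four-group × time test (15 df): power 0.603.
- Unadjusted postoperative mean (3 df): 0.873.
- Baseline-adjusted postoperative mean (3 df): 0.987.

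About 27 points come from averaging over visits and about 11 from baseline adjustment. At a group SD of 0.30σ and N=164, the 15-df test still has 0.909, so the dilution matters mainly for smaller effects.

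**The case against.** The strongest reply is that the planned test does what it was sized to do. On inputs that reproduce 164, it reaches its 90% target and has 95.5% at the recruitment target. That stands. A reader might infer that the plan throws away much of the trial's power, but the protocol's own figures do not support this.

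A stark contrast can be built. With 164 patients, seven occasions, ρ=0.5 and a constant aDOC effect of 0.3 SD, power is 25% for the 18-df four-group × time test, 42% for aDOC × time and 91% for an adjusted 1-df contrast. Three things are wrong with leaning on it. That effect is an interaction of f = √(0.0225 × 6/49) = 0.052, about a third of the planned size; at f=0.15 with seven occasions both interaction tests exceed 99%. Table 1 does not list the pain rating at 3, 6 or 12 months, so seven occasions do not fit this outcome. And the unadjusted 1-df contrast already has 71%, so only the step from 71% to 91% is due to baseline.

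Other parts of the reply also hold. No section says that baseline is a level of the time factor; this is inferred from the reference to changes and from the visit schedule. A factorial repeated measures ANOVA can test aDOC, Video and their interaction, so the protocol does not commit itself to one four-group omnibus test. A group-by-time test is a legitimate answer to a question about outcome dynamics.

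A reader might also see bias in the rule "Participants with extensive missing data (e.g., no primary outcome data at any timepoint) will be excluded from the respective analysis". Its one example describes patients who would contribute nothing to a mixed model either. The undefined word extensive is a minor drafting matter. Neither it nor the within-group tests are needed for this point.

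What the reply does not remove is that the article names its primary method and its comparison of changes, collects the baseline score and gives it no role as a covariate.

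**Conclusion.** The point holds as one of efficiency, not of validity or inadequate power. Against change scores, baseline adjustment would cut the variance by 25% at ρ=0.5, within a range of 35% to 15% for ρ from 0.3 to 0.7. At ρ=0.5 this raises power from 90.5% to 97.0% at 164 patients and from 95.5% to 99.0% at 200. These figures rest on m=2, ρ=0.5 and ε=1, which the protocol does not state, and on reading the primary test as one of change from baseline. Dilution across many time levels is a further, conditional loss: it depends on how many levels enter the test and on the effect being smaller than planned.

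**What to change.** Analyse the postoperative pain ratings with the T-4 rating as covariate, by analysis of covariance or a mixed model for repeated measures. State that the covariate is the value taken before the intervention (T-4a in the Table 1 legend), because the table's pain row says only T-4. Enter aDOC, Video and aDOC × Video as factors. Estimate each as a 1-df contrast averaged over postoperative visits named in advance, with a 95% confidence interval, and keep the interactions with time as secondary. Use the same model for the other continuous outcomes that have a T-4a value.

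The cost is a change of analysis wording and procedure, with no new data, visits or patients. The averaged contrast is less sensitive to an effect confined to one visit, which is the reason to keep the time interactions. The change should be fixed before unblinding.

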## Objectives and Outcomes

### Primary objective (subjective pain measure)

The primary objective of this study is to reduce postoperative pain by optimising preoperative treatment expectations. Pain will be assessed using a numerical rating scale (NRS 0–10) documented in a patient diary, and the Pain and State of Health Inventory (PHI). The PHI captures both pain intensity and the subjective experience over time, enabling a multidimensional evaluation of postoperative pain.

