### Secondary objectives

#### Subjective outcome measures

The secondary objectives include the reduction of postoperative functional impairments and evaluating the overall pain area, including its localisation and spatial extent, by distinguishing between interoceptive pain (bone/hip area) and exteroceptive pain (wound/surface).^33 34^

In addition, the study will investigate dynamic changes in the formation of patients’ expectations over time. Furthermore, we aim to clarify the role of self-efficacy in shaping these expectations both before and after surgery. Expectations will be analysed in terms of both an outcome (change over time) and potential moderation of the treatment effects on postoperative outcomes, such as pain and functional recovery.

The functional status and pain related to hip conditions will be assessed with the Harris Hip Score.^35^ The Quality of Recovery-15 questionnaire^36^ will be used to measure the quality of recovery, while the PHI^37^ will be used to quantify the impact of negative mood and distress on quality of life during the acute postoperative period. Self-efficacy will be evaluated using a modified, validated questionnaire measuring patients’ confidence in performing functional activities aligned with the study’s outcomes.^38 39^ This questionnaire has been validated for the study’s purpose and has been tailored to the study’s functional outcome measures. In addition, a general questionnaire on self-efficacy for arthritis,^40^ including hip OA, will be used. Surgery-related treatment expectations will be assessed using the Stanford Expectations of Treatment Scale (SETS),^41^ while postoperative pain management expectations will be evaluated with the GEEE tool^42^ and NRS scales to assess treatment expectations. Postoperative sickness symptoms and perceived treatment efficacy will be analysed using diverse questionnaires such as the Quality of Recovery-15.^31^ Finally, patients will rate the perceived credibility, warmth and competence of the study physician with the scale developed by Fiske *et al*,^43^ based on the “Stereotype Content Model” (SCM) as well as a specially developed questionnaire and the CARE-D questionnaire.^44 45^

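### Two instruments share the primary objective without an order, and LSD at an unadjusted 0.05 does not hold the 5% error rate among four arms once one arm truly differs.

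*Protocol article*

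**What the plan says.** All references are to the protocol article.

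- **Primary objective (subjective pain measure):** pain is measured by a 0–10 NRS "documented in a patient diary, and the Pain and State of Health Inventory (PHI"). Both instruments serve the primary objective. No order, co-primary rule or division of alpha is given.
- **Subjective outcome measures (secondary objectives):** the PHI appears again and "will be used to quantify the impact of negative mood and distress on quality of life during the acute postoperative period".
- **Abstract, Methods and analysis:** "The primary analysis will compare changes in pain intensity across groups", which is one outcome.
- **Sample size calculation:** the power analysis was "designed to detect interaction effects in a repeated measures ANOVA for the primary outcome of pain intensity", again one outcome, with no instrument named.
- **Statistical analysis:** "A two-sided p-value of <0.05 will be considered the threshold for statistical significance in all analyses". On follow-up tests, which depend on main and interaction effects being significant: "post hoc analyses (e.g., Least Significant Difference (LSD)) will be performed". The only correction mentioned, Greenhouse-Geisser or Huynh-Feldt, deals with sphericity and not with multiplicity.

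**The concern.** There are two separate defects.

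First, the primary endpoint is not settled. One section gives two instruments, two sections give one outcome, and one section lists the PHI as secondary. If both instruments count as primary, the trial could claim success on either, each at 0.05.

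Second, LSD makes no adjustment for the number of pairs. Placed behind a significant F test it protects the family-wise error for up to three groups, but not for four. Once one arm truly differs, the gate opens because of that arm, and the three equal arms are then compared with each other at 0.05 each.

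The second defect matters for the questions in *Study aims and questions*, which ask whether either component works and whether the combination does better. If only the combination works, exactly one arm differs. A false difference among aDOC, Video and TAU would then credit, or discredit, a component without cause.

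**Working it through.** **Inputs from the article:** four arms, 50 per arm, two-sided 0.05, f = 0.15, power 0.90, required n = 164; two instruments under the primary objective; LSD run only after significant effects.

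**Assumptions (not in the article):** NRS–PHI correlation 0 to 0.8; one change score per patient and instrument; a single four-arm F test as the gate; size of the true shift as listed below.

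**Step 1. The plan's own sample size.** For a within-between interaction, λ = f²·N·m/(1−ρ), df1 = (k−1)(m−1), df2 = (N−k)(m−1). The article does not state m or ρ. With k = 4, m = 2, ρ = 0.5 and N = 164, λ = 0.0225 × 164 × 2/0.5 = 14.76 on 3 and 160 df, and power is 0.905. The smallest N for 90% is 162, which rounds up to 164 for equal arms. The stated 164 is reproduced and is not in dispute.

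**Step 2. Two primary instruments, one four-arm test each, no true effect.**
- Independent: 1 − 0.95² = 9.75%.
- Correlation 0.5: 9.3% (simulation).
- Correlation 0.8: 8.0% (simulation).

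**Step 3. Size of the shift.** If one arm is shifted by d SD and three are equal, the variance of the four means is d² × (1/4)(3/4) = 3d²/16, so f = d√3/4.
- f = 0.15 read as an effect on the analysed score: d = 0.15 × 4/√3 = 0.35 SD.
- f = 0.15 read through Step 1: λ/N = 14.76/164 = 0.09, so f on the change score is √0.09 = 0.30 and d = 0.30 × 4/√3 = 0.69 SD.
- A shift of 1 SD corresponds to f = 0.43 and serves as an upper case.

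**Step 4. False differences among truly equal arms, one instrument.** Simulation with 50 per arm, 196 error df and 400,000 runs. LSD is gated by the four-arm F test at 0.05; Tukey and Holm cover all six pairs.

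| True shift of one arm | Gate opens | Gated LSD | Tukey | Holm |
|---|---|---|---|---|
| none | 5.0% | 5.0% | 5.0% | 4.1% |
| 0.35 SD | 40% | 9.4% | 2.8% | 2.7% |
| 0.69 SD | 95% | 12.1% | 2.7% | 3.6% |
| 1 SD | 100% | 12.2% | 2.8% | 4.3% |

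Gated LSD holds 5% in the first row only. Tukey and Holm do not exceed 5%, beyond simulation error, in any row.

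**Step 5. Price of the stricter method.** The standard error of a difference between two arms is √(2/50) = 0.20 SD. The smallest pairwise difference reaching significance is 1.97 × 0.20 = 0.39 SD with LSD, 2.59 × 0.20 = 0.52 SD with Tukey, and 2.67 × 0.20 = 0.53 SD at Holm's first step.

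**The case against.** **LSD is only an example, and an analysis plan may settle the method.** This is true and limits the point. But LSD is the only post hoc method named, and it stands beside a sentence fixing 0.05 for all analyses. A later plan that adjusts for multiplicity would have to depart from that sentence. This is a stated choice, not an omission.

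**The PHI may not be a second primary outcome.** This is also fair. The abstract and the sample size section speak of one outcome, and the secondary section uses the PHI for mood and distress. If the PHI is secondary, the 8–10% falls away. The contradiction with the primary objective section then still needs correcting, and the LSD point is untouched.

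**The factorial tests come first.** In a 2×2 design the component and synergy questions are answered mainly by the two main effects and the interaction. A main effect has two levels, so LSD adds nothing there. The LSD point therefore concerns comparisons between the four cells only. Leaving the two main effects unadjusted against each other is a defensible convention and is not criticised here.

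**Two stronger readings are tempting, and the article supports neither.**
- A reader might infer that the F test and LSD are repeated at each of six postoperative visits, which would give roughly 43% at a between-visit correlation of 0.5. The article plans a repeated measures ANOVA in which the visits enter one model, and Table 1 does not schedule the pain NRS at six postoperative visits.
- A reader might infer a 20% error rate from six unadjusted pairwise tests. That ignores the stated condition that significant effects come first.

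**Conclusion.** The point holds in limited form and should be corrected before the data are analysed.

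- **Endpoint:** the status of the PHI is contradictory. If both instruments are primary at 0.05, the chance of at least one false claim is about 8–10%, depending on a correlation that the article does not give.
- **Post hoc method:** gated LSD among four arms of 50 gives about 9–12% false differences among three equal arms when the fourth truly differs by 0.35 to 1 SD. Under the complete null it stays at 5%.

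The second result rests on one instrument, one score per patient and a single four-arm F test as the gate. That gate is favourable to the plan: if any one of the three factorial tests were enough to open LSD, the rate would be 11.8% even with no true effect. Neither result calls the sample size of 164 or the target of 200 into question.

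**What to change.** 1. In the primary objective section, name diary NRS pain intensity as the single primary outcome, in line with the abstract and the sample size section, and make the PHI wholly secondary.
2. Keep the planned repeated measures factorial ANOVA as the primary test at 0.05, including the interaction on which the sample size rests.
3. Replace LSD for the four-arm cell comparisons by Tukey or Holm over all six pairs, or by Dunnett if only the comparisons with TAU are to be tested.
4. Limit the 0.05 claim to the primary test and the adjusted comparisons. Report secondary outcomes with 95% confidence intervals and state that they are not confirmatory.

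**Cost:** a change of wording, with no extra patients and no change to the primary test or its power. Pairwise claims become harder: with Tukey, two arms of 50 must differ by about 0.52 SD instead of 0.39 SD to reach significance.
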